### Trial organization, quality control, registration and ethical aspects

The trial was designed at the Study Center of the German Surgical Society (Studienzentrum der Deutschen Gesellschaft für Chirurgie, SDGC) in cooperation with the Institute of Medical Biometrics and Informatics (IMBI) at the University of Heidelberg, Medical School. Trial monitoring is done by an independent monitor of the SDGC. The trial is performed according to the Declaration of Helsinki in its current German version and the Good Clinical Practice (GCP). Before trial start the independent ethic committee gave a positive vote on January 7^th^, 2004. All participants will be informed about the trial and the written informed consent must be signed before randomization. The trial was registered in December 2003 at the International Standard Randomized Controlled Trial Number Registration (ISRCTN96901396).

Two Amendments were accepted before this publication by the ethical committees: in the first amendment two additional secondary objectives (total time of the procedure, weight of specimen) were added. This was done in order to improve evaluation of the primary objective 'resection time' which is calculated by measuring the time between the completion of ligation of the upper pole vessels and the time of removal of the complete specimen. The second amendment was introduced to expand the inclusion criteria in regard to the type of operation. Until then, only hemi-thyroidectomies in combination with subtotal thyroid resection of the other side were included into the trial. Since this operation is not the only standard surgical procedure in goiter surgery in Germany, complete thyroidectomy and near-total thyroidectomy were added. The surgical details of these techniques are not in conflict with the objectives of the study. By this second amendment a shorter recruitment period is expected.

### Current status and duration of the trial

Up to now six centers are initiated and 155 patients, of the 400 needed, were randomized by five centers (status July 5^th^, 2006, details see acknowledgements). The first patient was randomized on March 5^th^, 2004. The expected recruitment period will last until the end of 2008.

## Discussion

The evaluation of optimal surgical therapeutic options and procedures should be performed according to the best current knowledge. Due to the principles of Evidence-based Medicine (EbM), the randomized controlled trial (RCT) is assumed to be the gold standard in evaluating different medical methods and procedures. Even in RCTs, though, the risk of bias should not be underestimated. In surgical trials a double blinded trial design is difficult to establish; therefore, the patient selection, power, randomization, surgeon's skill, data assessment and documentation of outcome measures and statistical analyses are important design issues and susceptible to the different forms of bias. Hence, all these issues are specified in the trial protocol a priori.

Selection bias. To minimize the selection bias all patients scheduled for thyroid surgery are screened consecutively in all participation sites. Moreover, neither patient age nor the size of the goiter is an exclusion criterion. Screening lists and case report files are monitored by independent investigators from the SDGC to ensure correct patient recruitment and meticulous documentation.

Randomization bias. Randomization is done in a block randomization system with alternating block sizes to avoid positive prediction of the last procedures in each block. The calculated randomization sequence is sealed at the IMBI for each participating center. Envelopes are nontransparent and cannot be resealed after opening. After exploration of the thyroid gland and affirmation of the indication an intra-operative randomization is performed. The unclosed randomization sheet is sent via fax to the IMBI.

Surgeon's expertise bias. Another source of bias is the surgeon's expertise. Most often new surgical techniques or methods are introduced by the most experienced surgeons. To minimize this source of bias stratification for surgeon's skill is made, and measured data will be analyzed by analysis of variance in regard to surgeon's skill, center and vessel occlusion technique. Due to this analysis of variance, bias of center effects and surgeon's skill should be reduced. Possible complications such as bleeding, re-operation due to bleeding, recurrent palsy or impaired function of parathyroid glands are assessed by blinded study nurses or investigators. Re-operation, recurrent palsy and impaired function of parathyroid glands are obvious events that can not be diminished by the responsible surgeon.

Prevention of non-conclusive results. Recent reports comparing different methods of hemostasis in thyroidectomies were underpowered or not designed as RCTs. In the calculation of the sample size of 420 patients, a post randomization drop out of 10 patients in each allocation arm and additional 40 patients for each secondary endpoint for 'lost to follow up' are included. Thus, the calculated sample size is large enough to draw definite conclusions. The interpretation of the hypothesis has a high statistical power: a significant result of this relevance test is equivalent to a time difference of at least 15 minutes [19].

Publication bias. One important tool to avoid bias in clinical trials is the international registration and publication of trial protocols. CLIVIT was registered in 2003 before the subsequent requirement of the International Committee of Medical Journal Editors were published [20].

In conclusion, this is the first randomized controlled multicenter relevance trial comparing different vessel occlusion techniques in thyroid surgery with adequate power and sufficient detailed information about the design as well as framework. If significant, the results might be generalized and may change the current surgical practice.

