### Sample size

A relevant difference between the two operations is defined as greater than 15 minutes. The expected difference is 20 minutes. Analysis of retrospective data showed a standard deviation of about 27 minutes for the whole operation. For the primary endpoint a percentage of 70% of the whole operation time is assumed. If this percentage were exactly 70% for every operation, standard deviation for the primary endpoint would be 0.7*27 min = 18.9 minutes. Since this relation will probably not be so strict, the standard deviation for the primary endpoint is estimated to be higher. Thus, a standard deviation of 20 minutes is assumed. The α level is set to 0.05; therefore, 200 patients per group are required to obtain a power of 80% (β = 0.2) using a simple one-sided t-test for two groups with a shifted null-hypothesis. Due to the fact that no interaction is expected regarding surgeon experience and treatment group, the sample size calculation is also valid for the ANOVA model of the primary analysis. In order to incorporate an expected early dropout rate of 5%, a total of 420 patients is required.

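### The Discussion says 420 includes 40 further patients per secondary endpoint, but 420 is only 400 plus 5% dropout, and the status section counts randomized patients against 400

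*Protocol article*

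**What the plan says.** The Sample size section of the protocol article sets the threshold for the shifted null hypothesis: "A relevant difference between the two operations is defined as greater than 15 minutes". It expects a difference of 20 minutes and assumes a standard deviation of 20 minutes. "The α level is set to 0.05", and "200 patients per group are required to obtain a power of 80" per cent, "using a simple one-sided t-test for two groups with a shifted null-hypothesis". It then moves from evaluable patients to the total: "In order to incorporate an expected early dropout rate of 5%, a total of 420 patients is required". It makes no allowance for secondary endpoints.

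The Discussion, in its paragraph on preventing non-conclusive results, describes the same 420 differently. It says the calculation includes "a post randomization drop out of 10 patients in each allocation arm and additional 40 patients for each secondary endpoint" to cover loss to follow-up. The next sentence draws the inference that "the calculated sample size is large enough to draw definite conclusions".

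The section on current status reports "155 patients, of the 400 needed, were randomized by five centers". The Abstract counts randomized patients against a requirement of 420. The Statistical analysis section assigns descriptive statistics to the secondary endpoints.

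**The concern.** The article explains 420 in two incompatible ways. In the Sample size section the step from 400 to 420 is early dropout and nothing else. In the Discussion the same 420 is said to hold a further 40 patients for every secondary endpoint. Both cannot be true, and the second account is the stated ground for an assurance about how conclusive the trial will be.

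The recruitment target is also given as two numbers. The status section sets randomized patients against 400, which in the Sample size section is the number to be evaluated, not the number to be randomized. Recruitment was still running at the time of writing, so the target should be unambiguous.

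At stake is what a reader takes from the article. The secondary endpoints include recurrent nerve paralysis, reoperation for bleeding and impaired parathyroid function. A reader told that a follow-up reserve was built in could believe that these endpoints were allowed for in the calculation. The article also says it was published to lay its starting assumptions open, so its account of the sample size should be consistent.

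**Working it through.** **Inputs**, all from the Sample size section: threshold 15 min, expected difference 20 min, so the distance from the null is 20 − 15 = 5 min; standard deviation 20 min; one-sided α = 0.05; power 80%; equal groups; early dropout 5%.

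**Step 1: reproduce the 200 per group.** By the normal approximation, n per group = 2 (z₀.₉₅ + z₀.₈₀)² σ² / δ² = 2 × (1.645 + 0.842)² × 20² / 5² ≈ 198. The exact noncentral t calculation gives 199. At 200 per group the noncentrality is 5 / (20 × √(2/200)) = 2.5 and the power is 80.3%. The stated 200 is correct. A two-sided test at 0.05 would need 252 per group, so the one-sided reading is the one used.

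**Step 2: reproduce the 420.** 2 × 200 = 400, and 400 × 1.05 = 420. Dividing by 0.95 instead and rounding up to an even number gives 422; the difference is immaterial.

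**Step 3: account for the margin.** 420 − 400 = 20, which is 10 per arm. This matches the first part of the Discussion's sentence exactly. What remains for the additional 40 is 20 − 20 = 0.

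**Step 4: what including the 40 would imply.** The article does not say whether the 40 are in total or per arm, so both are shown.

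| Reading of the 40 | Total needed to keep 400 evaluable | Evaluable if 420 is kept | Power of the primary test at that number |
|---|---|---|---|
| In total | 400 + 20 + 40 = 460 | 420 − 20 − 40 = 360 (180 per group) | 76.5% |
| Per arm | 400 + 20 + 80 = 500 | 420 − 20 − 80 = 320 (160 per group) | 72.1% |

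Neither reading fits 200 per group with 80% power and a total of 420. The power column only tests whether the Discussion's account could be the true derivation. It does not predict the power of the primary test.

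**Step 5: the target of 400.** If recruitment ended at 400 randomized and 5% dropped out, 400 × 0.95 = 380 would be evaluable, or 190 per group. The exact t power is then 78.4%, against 80.3% at 200 per group.

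**The case against.** The strongest reply is that the sentence about the 40 describes tolerated losses, not added patients. The 400 is a requirement of the primary test only. The secondary endpoints are descriptive and have no required number, so 420 patients could lose 20 early and another 40 at follow-up without breaching any stated requirement. That is sound as a description of what the trial can bear. It does not rescue the text, which says that the 40 are included in the calculation of 420. The calculation shown contains no such item.

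It can also be said that 400 in the status section means evaluable patients. That is possible, but the sentence counts randomized patients against it.

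Several stronger readings are tempting, and the documents do not support them:

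- *The reserve does not exist at all.* The 10 per arm exists, exactly.
- *The primary test is underpowered.* The primary endpoint is a time interval within the operation, so loss to follow-up cannot reduce it. The planned 80% holds under the stated assumptions if 420 are randomized and dropout is as expected.
- *Recruitment will stop at 400.* Nothing says so, and three other places give 420. Even then the loss is about 2 percentage points. It may be less, because patients enter the intention-to-treat population once the upper vessels are cut, which follows intraoperative randomization.
- *The trial is too small for its complication endpoints.* The article gives no complication rates to calculate from, and how these endpoints are to be reported is a matter for an analysis plan that is not shown. All that can be said is that the article states no calculation for them.

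**Conclusion.** The point holds as a misstatement of what the sample size contains, together with an inconsistent recruitment target. The whole margin of 20 patients is used by early dropout, and none of the further 40 per secondary endpoint is in the 420. Including them would take at least 460. Counting to 400 randomized instead of 420 would cost about 2 points of power (78.4% at 380 evaluable, against the planned 80%).

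The primary calculation is correct and unaffected if 420 are randomized. The part of the Discussion's assurance without support is the part that leans on the follow-up reserve, which concerns the secondary endpoints. The power figures rest on the article's own inputs (5 minutes beyond the threshold, standard deviation 20 minutes, one-sided 5% test, equal groups). The 380 also assumes that the stated 5% dropout applies to 400 randomized.

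**What to change.** 1. Give one account everywhere: 420 to be randomized, 400 evaluable for the primary endpoint. In the status section, count randomized patients against 420.
2. In the Discussion, delete the statement that 40 further patients per secondary endpoint are part of the 420. Alternatively, restate it as an expected loss that leaves fewer patients for follow-up endpoints, and say whether the 40 are in total (360 remaining) or per arm (320 remaining).
3. Limit the claim that the sample is large enough for definite conclusions to the primary relevance test, under the assumed 20-minute difference and 20-minute standard deviation.

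The cost is wording only. No patients are added, and no test or analysis changes. The published assurance becomes narrower.
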